# A full-factorial randomized controlled trial of adjunct couples HIV testing and counseling components addressing drug use and communication skills among sexual minority male couples

**DOI:** 10.1186/s12889-021-12208-3

**Published:** 2021-11-24

**Keywords:** Club drugs, Gay and bisexual men, Men who have sex with men, Relationships, Emerging adults

## Abstract

**Background:**

The past decade has seen increasing attention directed to the development of HIV prevention interventions for male couples, driven by epidemiological data indicating that main or primary – rather than causal – partnerships account for a substantial number of HIV infections in this population. Couples HIV testing and counseling (CHTC) has emerged as a standard of care in the US. This protocol describes a study that aims to evaluate the efficacy of two adjunct components to CHTC – communication training (CT) videos and a substance use module (SUM) – to reduce drug use and sexual HIV transmission risk behavior.

**Methods:**

Eligible couples must include one participant who is aged 17-29, HIV-negative, and reports recent drug use. Both partners must be aged 17 or older, identify as cismale (assigned male sex at birth and currently identify as male gender), and communicate in English. Couples are randomized post-baseline to one of four conditions (CHTC as usual, CHTC plus CT video; CHTC + SUM and CHTC + CT video + SUM) in a full-factorial design. Follow up assessments are completed at 3-, 6-, 9- and 12-months post baseline.

**Discussion:**

Results of this trial will enhance the application of CHTC. If found effective, adjunct components would comprise a brief and scalable drug use intervention that could be readily integrated into existing HIV testing settings.

**Trial registration:**

ClinicalTrials.gov Protocol Registration; NCT05000866; completed August 3, 2021; https://register.clinicaltrials.gov/

Protocol version 1.0; September 1, 2021.

## Introduction

### Background

For a little more than a decade, considerable attention has been focused on the sexual health needs of sexual minority men (SMM) in same-sex relationships (including gay, bisexual and other men who have sex with men). The impetus for much of this work was provided by groundbreaking research that estimated 35-68% of new HIV infections among SMM were transmitted between main – or primary – relationship partners rather than casual sex partners [2, 3, 32]. Risk for main partner HIV infection was particularly high among younger SMM, with estimates as high as 79% among those aged 18-29 years [32]. These studies suggested that main partner HIV transmission risk may arise from the fact that SMM have sex with their main partners more frequently and are less likely to use condoms when having sex with their main partner. More recently, [name] et al. [28] identified that partnered SMM are more likely to have sex with casual partners on days they also have sex with their main partners. The co-occurrence of these behaviors may also enhance shared risk for HIV.

In response to the observed need for dyadic sexual health interventions for this population, couples HIV testing and counseling (CHTC) – originally developed for heterosexual couples in African nations with generalized epidemics – was adapted for use with male couples in the United States [4, 30]. CHTC is an 8-step intervention during which couples receive an HIV test together and learn their status together. The HIV tester also engages the couple in a discussion that reviews their current HIV prevention practices, clarifies their sexual agreement – and expectations around communication if the agreement were broken – and develops a shared HIV prevention plan with the couple.

More recent research supports the need for ongoing attention to this population. Evidence suggests that single SMM and those in non-monogamous relationships (where sex with casual partners is in some way permitted) engage in condomless anal sex (CAS) with casual partners at comparable rates [22, 26]. Furthermore, there are indications that SMM in monogamous relationships (wherein partners have agreed to forego sex with partners outside their relationship) who break their agreement and engage in CAS with casual partners may actually do so more frequently than non-monogamous and single men [22].

The use of illicit drugs has been consistently linked to sexual risk taking among SMM. In particular, the use of a number of illicit drugs (i.e., cocaine or crack, methamphetamine, ecstasy, ketamine, gamma-hydroxybuterate – GHB) has been associated with either the occurrence or frequency of CAS with casual partners across a range of studies (e.g., [1, 15, 16, 22, 23]). In their recent paper, [name] et al. examined data from a sample of more than 65,000 SMM and found that this association was significant across relationship status and sexual agreements, though it was significantly stronger among single and non-monogamous men compared to those in monogamous relationships [22]. Separately, [name] et al. [28] have since observed an association between illicit drug use and CAS with casual partners in day-level data obtained from male couples.

[name] et al. [20] posited that CHTC – which in its standard form involves the negotiation of a sexual agreement and joint HIV prevention planning – might provide an opportunity for male couples to develop consensus related to rules or limitations on drug use. Furthermore, they hypothesized that augmenting CHTC with supplemental communication skills training might also enhance its efficacy. The team developed a communication training (CT) video to deliver dyadic skills training following a standard Cognitive Behavioral modeling paradigm. They also developed a substance use module (SUM) wherein partners create a calendar feedback tool, which is subsequently debriefed using a brief dose of Motivational Interviewing (MI). The MI component is delivered following the framework for couples MI derived by [name] et al. [24, 27].

Initial pilot results [20] indicated that completion of the SUM alone was associated with statistically significant decreases in the odds of drug use (*B* = − 3.62; *p* = .03) and drug use related problems as measured by the Drug Abuse Screening Test (DAST-10) [17] (*B* = − 0.75; *p* = .02) at 1-month post-intervention. While CT videos were not independently associated with reductions in drug use or DAST-10 scores; they significantly enhanced the long-term benefits of SUM completion. At 3-month and 6-month follow-up the SUM was only associated with significant decreases in the odds of drug use (*B* = − 2.79; *p* = .013 and *B* = − 3.93; *p* = .014 respectively) and DAST-10 scores (*B* = − 0.64; *p* = .01 and *B* = − 0.79; *p* = .003 respectively) among men who viewed the CT videos. In a direct comparison between the CHTC as usual condition and those participants who received both *We Test* adjunct components (CHTC+SUM+CT video), the combined condition had significantly lower odds of drug use at 1- and 3-month follow up and significantly lower DAST-10 scores at all follow-up time-points.

While promising, the results of [name] et al. [20] were limited in several ways. First, their study did not include biological markers for drug use and sexual risk taking to validate self-report responses. Second, the most distal follow-up was 6-months post-intervention. This was not sufficiently long enough to observe decay in the treatment effect for substance use outcomes. This limited the development of guidance or recommendations on the timing of CHTC-retesting with *We Test* module delivery. The next step in this program of research is to conduct a full scale efficacy trial that incorporates the use of biological markers in addition to self-reported behavioral data and a more extensive follow-up period with an expanded potential to observe decay in the intervention effect.

### Objectives

The purpose of the current study is to evaluate the efficacy of CT and SUM adjunct modules that augment the existing CHTC protocol. Our primary hypotheses are that completion of the SUM will be associated with a statistically significant decrease in drug use and drug-related problems at all follow-ups. We also hypothesize that viewing CT videos will enhance the effect of SUM. Based upon our initial results, we anticipate that there will not be a direct effect of adjunct intervention components on HIV Transmission Risk Behavior (TRB); however, we have powered the study to examine indirect effects. We therefore propose secondary hypotheses in which the SUM and CT components significantly reduce sexual HIV transmission risk behavior as a result of decreases in drug use.

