#### Sample size

Power analyses were generated by Monte Carlo simulation using Mplus (version 8.0). All estimates were based upon 10,000 sample replications and power was defined as the percentage of randomly generated samples in which the specified parameter was statistically significant. All simulated models were multi-level, nesting participants (at Level 1) within couples (at Level 2). Models focused on detecting between-condition differences at any one follow-up time-point (as opposed to predicting slope factors). This allowed for more direct extrapolation of error variances from existing baseline data and is consistent with the primary aim of the study. The main effects of the two interventions (the drug use calendar and video-based communication skills training) as well as their interaction were modeled at level 2. Based upon the results of our previous studies, we anticipate 80% minimum follow-up retention at 12 months. These analyses therefore reflect a conservative analytic sample of 240 couples (480 individuals).

Analyses indicated that the proposed study has power > .80 to detect a simple main effect of SUM and/or CT videos corresponding to a 15% reduction in the odds of drug use and a 1.0 point reduction in DAST scores at any follow-up time point. The proposed study has power > .80 to detect a 2% reduction in the odds of reporting HIV TRB. Effects of these magnitudes are plausible given our pilot data. *We Test* pilot data have indicated that mediational pathways linking CT videos with drug use outcomes likely involve depression. The effects of viewing ACTV were generally small across indices of communication skills and psychological functioning. The most promising (statistically significant) effects were associated with improvements in self- disclosure communication (β = .13) and depression (β = −.16). Notably, the indirect pathway between CT and depression through self-disclosure communication was of moderate size (β = −.12) indicating that communication skills may be one mechanism by which ACTV yields reductions in depression. Depression scores were, in turn, positively associated with the odds of drug use (β = −.45) and DAST scores (β = .06). Using these effects as preliminary estimates, Monte Carlo simulations suggested that the proposed study design has power > .80 to detect the significance of direct pathways and implied indirect effects of intervention.

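### The claim that the study is powered for indirect effects is not supported for the secondary hypothesis (SUM/CT → drug use → TRB): the only indirect-effect power described is for a different chain

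*Protocol article*

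**What the plan says.** **Objectives.** The investigators expect no direct effect of the add-on components on TRB, but state that "we have powered the study to examine indirect effects". They then propose, as following from this, "secondary hypotheses in which the SUM and CT components significantly reduce sexual HIV transmission risk behavior as a result of decreases in drug use". The exposures are SUM and CT, the mediator is drug use and the outcome is TRB.

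**Sample size.** Three separate power statements are made for 240 couples (480 men):

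- Power > .80 for a main effect of SUM and/or CT: 15% lower odds of drug use and 1.0 point on DAST.
- Power > .80 for a 2% reduction in the odds of reporting TRB. No mediator is named.
- For mediation, "mediational pathways linking CT videos with drug use outcomes likely involve depression". The coefficients listed are CT on self-disclosure (.13), CT on depression (−.16), CT on depression through self-disclosure (−.12), and depression on drug use (−.45) and on DAST (.06). The conclusion follows from these: "Using these effects as preliminary estimates, Monte Carlo simulations suggested that the proposed study design has power > .80" for the direct pathways and the indirect effects they imply.

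**Moderation/mediation analyses.** The last paragraph lists drug use as a mediator of sexual risk outcomes under follow-up exploratory analysis.

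**The concern.** The Objectives section uses power for indirect effects as the reason for the TRB hypothesis. The mediation power under Sample size has CT as its exposure, self-disclosure and depression as its mediators, and drug use or DAST as its outcome. Drug use is the end of that chain, whereas in the hypothesis it is the mediator. Power computed for one chain does not carry over to another that needs a further path.

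The interpretation of the TRB result is at stake. Because no direct TRB effect is expected, drug use is the route by which the plan expects to affect TRB. A null mediation result from a study described as powered for it could be taken as evidence against the mechanism, although no power for that mechanism is documented. The document also gives this test two ranks, secondary in Objectives and exploratory in the mediation section.

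**Working it through.** **1. The chains side by side**

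| | Hypothesis (Objectives) | Mediation power (Sample size) |
|---|---|---|
| Exposure | SUM and CT | CT |
| Mediator | drug use | self-disclosure, depression |
| Outcome | TRB | drug use, DAST |
| Drug use → TRB path | needed | not given |

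The mismatch is textual. The arithmetic below shows only how much depends on it. The Mplus runs cannot be repeated, because alpha, base rates, within-couple correlation (ICC) and residual variances are not given. Two-sided .05 is assumed throughout.

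**2. The plan's own mediation figure**

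For a standardized β, SE = √((1−β²)/(n−2)) and power = Φ(|β|/SE − 1.96), with n between 240 (couples) and 480 (men) and absolute values used.

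- CT → depression, β = .16: power .71 to .94. At n = 480, SE = √(.9744/478) = .0451, .16/.0451 = 3.54 and Φ(1.58) = .94.
- Depression → drug use, |β| = .45: about 1.0. Depression → DAST, β = .06: .15 to .26.
- Product of the two paths: .71 to .94 for drug use, .11 to .25 for DAST.

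On this approximation > .80 is attainable for CT → depression → drug use towards 480 independent men, but not for DAST. Neither figure concerns TRB.

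**3. The TRB sentence (2% lower odds)**

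For two proportions with n men per factorial margin (240, or 240/(1+ICC)), power = Φ((d − 1.96·SE0)/SE1), plus the opposite tail where it matters. SE0 uses the pooled variance and SE1 the separate variances.

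- OR .98 at 50% TRB: p = .98/1.98 = .4949, d = .00505, SE0 = SE1 = .0456. First tail Φ((.00505 − .0895)/.0456) = Φ(−1.85) = .03, opposite tail .02, total about .05. This equals the false-positive rate.
- Read as 2 percentage points: about .07 to .12 for TRB between 50% and 10%, and .35 if TRB were as rare as 3%.

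Neither reading reproduces > .80.

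**4. First path, SUM → drug use**

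- 15% lower odds at 50% use: p = .85/1.85 = .4595, d = .0405, SE0 = SE1 = .0456. Φ((.0405 − .0894)/.0456) = Φ(−1.07) = .14. With ICC .5 this is .11. At 90% use with independent men it is .08.
- 15 percentage points, 50% to 35%: d = .15, SE0 = .0451, SE1 = .0446. Φ((.15 − .0885)/.0446) = Φ(1.38) = .92. With ICC .3 it is .83, and with ICC .5 it is .78. A fall from 65% to 50% gives nearly the same values.

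**5. Full chain, joint-significance test**

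Indirect power ≈ power(first path) × power(second path), so it cannot exceed the weaker path. The second path assumes 480 independent men, 50% drug use and 20% TRB in non-users. At OR 2, for example, TRB in users is .333 and power is .91.

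| Drug use → TRB OR (assumed) | Second-path power | First path .14 (OR .85) | First path .83 (15 points, ICC .3) | First path .92 (15 points, ICC 0) |
|---|---|---|---|---|
| 1.25 | .17 | .02 | .14 | .16 |
| 1.5 | .47 | .07 | .39 | .43 |
| 2 | .91 | .13 | .76 | .84 |
| 3 | 1.00 | .14 | .83 | .92 |

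**The case against.** **The TRB sentence may be the implied indirect effect.** With OR .85 on drug use and an assumed drug use → TRB OR of 1.5 to 2 (same base rates), the implied TRB OR is .984 to .973, close to a 2% reduction. This is possible, but the text names no mediator and does not call the effect indirect, and > .80 is not reproducible for an effect of that size.

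**SUM is powered.** A reader might infer that SUM is missing from the power section. It is not: SUM/CT → drug use, the first half of the hypothesis, has its own statement. What is absent is the second half and the combination. The Background describes links between drug use and condomless sex with casual partners but gives no effect size, and the TRB indicators are narrower (absence of PrEP, detectable viral load, STI diagnosis).

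**Power may be adequate.** A reader might infer that power is shown to be below .80. The documents do not support that. The pilot SUM coefficients (B = −2.79 to −3.93, the later ones only among CT viewers) are far larger than OR .85. The planned growth models use five time points, whereas the calculation here uses one, as the power section does. Two paths with power .90 each would give .81. The low figures under OR .85 reflect a weak main effect, which would remain a problem even if the right chain had been simulated.

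**Mediation is not the only TRB analysis.** TRB is a listed primary outcome and is also tested directly.

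**An article condenses the protocol.** Unprinted inputs alone would be no finding. Here the article asserts power and describes a simulation of another chain, and that stands.

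**Conclusion.** The point holds as a mismatch between a stated power and the hypothesis it is used to justify. The mediation figure of > .80 belongs to CT → self-disclosure/depression → drug use/DAST. No power is reported for SUM/CT → drug use → TRB, and the separate TRB statement does not supply it (about .05 at OR .98 with 240 v 240 men).

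The size depends on two things the article leaves open. If 15% means lower odds, the first path caps indirect power at about .08–.14. If it means percentage points, the result turns on the unstated drug use → TRB path, and about .80 needs an OR of roughly 2 with independent partners, or between 2 and 3 with ICC .3. Alpha, base rates, ICC and the second path are assumptions. The conclusion is that the power is unsupported for this hypothesis, not that it is inadequate on every reading. The conflict between secondary and exploratory status needs no assumption.

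**What to change.** - **Objectives:** limit the power statement to the chain that was simulated, and stop using it as the basis for the TRB hypothesis. Reconcile the secondary status given there with the exploratory status under Moderation/mediation analyses.
- **Sample size:** run the Monte Carlo for SUM/CT → drug use → TRB over a stated range of drug use → TRB paths, saying whether 15% and 2% are relative odds or percentage points. Report the resulting power, or the smallest indirect effect detectable with .80 power at 240 couples.
- **If power is below .80:** say so, and report the TRB mediation as an estimate with a confidence interval.

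The cost is one further simulation, a few reworded sentences and probably a less favourable stated power. Enrolment and procedures do not change.

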## Methods

### Trial design

This study utilizes a randomized controlled trial design to evaluate the efficacy of two adjunct intervention components for couples HIV testing and counseling (CHTC). Participants are randomized in a full-factorial design to one of 4 conditions: CHTC as usual; CHTC + CT videos; CHTC + SUM; or CHTC plus both adjunct components.

### Rationale for comparison condition

The use of CHTC as usual, as opposed to a no-treatment control reflects the status of CHTC as the standard of care for HIV testing among partnered SMM [34].

### Study setting

All research staff are based in university research centers at Hunter College of the City University of New York or the University of Michigan, Ann Arbor. All study assessments and intervention sessions are conducted remotely via Health Insurance Portability and Accountability Act (HIPAA)-compliant, video conferencing software. Participants must reside in either the New York, NY or Detroit metropolitan areas and have access to a device capable of conducting remote study visits.

### Eligibility criteria

Participants must fulfill the following inclusion criteria to be enrolled in the study. In each couple, both partners must indicate cismale gender and be 17 years of age or older. In addition, at least one participant in each couple must (1) be aged 17 to 29 years; (2) self-report an HIV-negative or unknown sero-status; (3) report use of at least 1 illicit drug (cocaine/crack, opiates, misuse of prescription medication, stimulants, psychedelics, ecstasy, ketamine, GHB) in the past 30 days, (4) have engaged in CAS with a casual partner or a main partner who is non-monogamous or sero-discordant in the past 90 days, (5) live in the New York City or Detroit metropolitan area, and (6) be able to speak and read in English.

Participants will be excluded from the study if they indicate signs of acute suicidality; gross impairment in cognitive functioning; or any history of intimate partner violence and current safety concerns in the current relationship. The trial does not place restrictions on concomitant receipt of care for substance use or HIV prevention.

### Interventions

All participants, regardless of condition, will complete a CHTC session. Completion of CHTC involves 8-steps: 1.) Introduce CHTC and Obtain Concurrence: an introduction to the CHTC process and receiving the couples consent; 2.) Prepare For and Conduct HIV Test: explanation of the HIV test itself and possible results couples could receive, followed by a rapid HIV test; 3.) Explore Couple’s Relationship: an exploration of the couple’s relationship to build rapport; 4.) Discuss HIV Risk Concerns and Reasons for Seeking CHTC: discussion of current risks, reasons for testing and HIV prevention strategies (i.e. condom use, PrEP use, etc.); 5.) Discuss Couple’s Agreement: exploration of the couple’s sexual agreement and rules in regards to outside sexual partners; 6.) Provide Results: results are given to each member of the couple at the same time and can be the same (concordant negative or positive) or discordant; 7.) Develop Care, Treatment, and Prevention Plan Based on Result: discussion of future steps regarding HIV transmission risk prevention strategies (i.e. discussion of introducing condoms or PrEP use); and 8.) Link with Follow-up Services: referrals given in light of current HIV test results (i.e. referrals for confirmatory testing and other health services).

### Communication training (CT) videos

The CT video component is designed to be self-delivered. Four couples are depicted in separate scenes discussing HIV testing, drug use, sexual agreements, and drug use during sex. Each scene is viewed twice. In the initial viewing, the couple in the video makes one or more communication errors. The scene is subsequently viewed a second time and the couple utilizes more effective communication skills, resulting in a more adaptive resolution. Each scene is introduced by a narrator who points out communication errors and orients viewers to skills utilized in adaptive versions of each scene.

### Substance use module (SUM)

The SUM is administered after step 5 of CHTC and prior to the delivery of rapid HIV-test results. The couple is first asked to fill in a calendar for the past 30 days, indicating each day on which either member used drugs or consumed alcohol. Completion of the calendar is done using an excel spreadsheet displayed on a shared computer screen to facilitate remote intervention delivery. After completion of the calendar, the HIV tester asks a series of debriefing questions designed to elicit the couples’ perspective on their use, establish the couple’s goals and limits for drug use, and make plans to achieve these goals.

